#### Online testing subgroups

A small subgroup of participants was afraid of COVID-19 infection during the pandemic. Thus, their cognitive testing was converted to an online examination to reduce personal contact time. The other data collection remained in person the same way as the rest of the participants because personal contacts were short. We wanted to have as many participants as possible with their measures: samples of biological material, questionnaires, physical fitness, and actigraphy.

### Probiotics and placebo

Participants were offered to take one probiotic/placebo tablet each day along with two fiber/placebo fiber tablets. The time of tablet consumption was up to the participant. More details about the content of the probiotic and placebo tablets are available in Supplementary material 2. All the tablets were provided by the company NEXARS (Brno, Czech Republic).

Participants were asked about the adverse side effects of the intervention at the end of each 3 months using a structured list of hypothetical side effects.

### Outcomes and measures

The effect of the probiotic intervention was evaluated using several comprehensive sets of cognitive tests, subjective questionnaires, visual scales, physical fitness, actigraphy, blood, urine, and stool samples.

#### Primary outcome measures

##### Cognitive measures

Cognitive function changes were assessed with brief tests and a neuropsychological battery, which took about 1 h on average. The reason was to show whether the influence of probiotics could be demonstrated with either approach or both. If proven, physicians and other professionals could utilize brief instruments in their practice to verify the favorable effect of probiotics. Seven raters were trained in all the tests by an experienced neuropsychologist. Each rater aimed to perform every cognitive evaluation of their participants for the whole clinical trial duration at all visits from the first to the fourth one to reduce assessment variability. Two versions of the cognitive battery were prepared, as participants were evaluated either in person or online. Firstly, we describe all tests for an in-person examination. Secondly, online versions of the tests follow and are explained. Table 1 shows a battery of tests and questionnaires administered in the same order at each testing session by the same rater throughout the clinical trial and their equivalents for online testing.

**TABLE 1 T1:** List of tests and questionnaires administered at all visits in-person and online.

In-person order number	Test/questionnaire name	Online order number
1	The Clock Drawing test (CDT)	–
2	The Amnesia Light and Brief Assessment (ALBA) test	1
3	The Category (animal) fluency test	3
4	The Rey Auditory Verbal Learning Test (RAVLT) trials A1-A6	2
5	Trail Making Test (TMT) parts A and B	−
6	The Digit Symbol subtest from the Wechsler Adult Intelligence Scale (WAIS-III)	−
7	An anamnesis questionnaire	+
8	Short form of Geriatric Depression Scale (GDS)	+
9	The Beck Depression Inventory, 2nd version (BDI-II)	+
10	The Beck Anxiety Inventory (BAI)	+
11	The Functional Activities Questionnaire (FAQ-CZ)	+
12	The Questionnaire of Adverse Events	+
13	The RAVLT trial A7 delay recall	7
14	In-house cognitive battery ABACO including the PICNIR test	5
15	A questionnaire regarding side-effects of probiotics	+
16	The Dietary Habits Questionnaire	+
X	The phonemic fluency test (with initial letters NKP)	4
X	The Digit Span subtest from WAIS-III	6
		

ABACO, Assessment Battery of Cognition; PICNIR, Picture Naming and Immediate Recall. In-person order numbers are on the left, online order numbers are on the right. Three tests (−) were not administered online. All questionnaires were completed in-person (+).

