##### Self-report subjective questionnaires of depression and activities of daily living

Participants filled in the Geriatric Depression Scale (GDS) and the Functional Activities Questionnaire (FAQ-CZ) to assess their mood in the last 3 months and activities of daily living at each visit. The GDS ranged from 0 to 15 points, and FAQ-CZ ranged from 0 to 30 points. The more points, the more answers to depressive content in the GDS and the more impaired activities of daily living in the FAQ-CZ (Pfeffer et al., 1982; Lesher and Berryhill, 1994; Lach et al., 2010).

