##### Biological surrogate markers of probiotic intervention

Serum, urine, and stool samples are taken for measurements of blood biochemistry, apolipoprotein E genotyping, metabolomic studies, and some brain-derived proteins and antibodies. The plan was to monitor metabolomics biomarkers, neurofilament light chain (NfL), and other measures and changes due to probiotic intervention. Participants provided their urine, fecal, and blood samples at each visit except the first one, as explained earlier.

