### Power calculation

Given our sample size, we will able to detect the effect size of Cohen’s d = 0.43 in the matched-pairs two-tailed *t*-test, assuming power = 0.8 and α = 0.05. This will be d = 0.51 in those tests when only in-person data could be used.

For between-group comparisons, we could detect the effect size of Cohen’s d = 0.59 in a two-sample two-tailed *t*-test, assuming power = 0.8 and α = 0.05. This would be d = 0.67, assuming the use of only in-person data.

All power calculations were performed in G*Power 3.1.9.7 Software (Faul et al., 2007). As we did not attain equal group numbers, the sensitivity of the matched-pairs *t*-test is computed for the smaller group. This means we could detect a slightly smaller effect size for larger groups than reported here.

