We chose an intervention using probiotics and prebiotics. A relationship between the gut microbiota and brain functions is considered in several diseases or conditions (Marotta et al., 2019; Salami, 2021; Handajani et al., 2022; Klann et al., 2022; Mukilan, 2022; Xiang et al., 2022). If proven effective, this natural way would be an easily feasible approach to prevent or postpone more pronounced memory decline or improve mood or anxiety in the elderly. In our comprehensive study, we decided to explore different aspects of brain functioning, physical performance, and blood, urine, and stool changes in response to probiotics with prebiotics. We use an explorative approach to determine which measures are influenced due to the intervention. We chose a crossover study design to ensure active intervention for each participant, which may achieve higher compliance and allow us to use each participant as a control for their own scores.

Probiotic treatment was intended for 3 months. A longer interval would prolong the duration of the study, make the trial more logistically complicated, and decrease participants’ compliance with the study. Three months of treatment was used in another related study (Handajani et al., 2022). The duration of our grant support also limits us. Our study was extended to 9 months for additional examinations to see the long-term effect of the intervention in a subset of participants.

The number of assessments and two types of tablets with a change after 3 months required careful management and sufficient and different personal resources and skills, facility equipment, and expert experience in many disciplines. We balanced recruitment with examinations and space capacities. This was the reason for establishing two centers for performing the study and limiting the number of participants included. Unfortunately, the COVID-19 pandemic complicated such a comprehensive clinical trial. Some participants refused to come to in-person assessments. The online testing had to be prepared for a relatively small group. Changing personal assessments to online ones might be an innovative approach to testing if a positive signal will be proven even in our small subgroups.

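### About 19 scored measures, plus biochemistry and metabolomics, share the primary tier with no ranking and no primary time point, while sensitivity is computed for a single test at α = 0.05

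*Protocol article*

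**What the plan says.** Five blocks of the protocol article sit under Primary outcome measures: the general text on cognitive measures, the brief tests, the neuropsychological battery, the GDS and FAQ-CZ questionnaires, and the biological markers. A separate Secondary outcome measures heading follows (BDI-II, BAI, visual scales, fitness), so the two tiers are deliberate.

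The stated purpose of running two kinds of cognitive test is: "The reason was to show whether the influence of probiotics could be demonstrated with either approach or both". The same paragraph adds that, if an effect is proven, clinicians could use the brief instruments to confirm it. For the biological markers: "The plan was to monitor metabolomics biomarkers, neurofilament light chain (NfL), and other measures and changes due to probiotic intervention". No measure, composite, order of testing or visit is singled out.

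Proposed analysis foresees unpaired t-tests at each time point or paired t-tests between time points. Cognitive outcomes are analysed separately for in-person and online participants, with the online results exploratory.

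Power calculation gives sensitivity for a single two-tailed test, "assuming power = 0.8 and α = 0.05". The detectable d is 0.43 (paired) and 0.59 (between groups) with all participants, and 0.51 and 0.67 in person only.

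The Discussion states: "We use an explorative approach to determine which measures are influenced due to the intervention".

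**The concern.** A primary tier with a power calculation and directional hypotheses (Figure 4 legend) tells readers that a significant result there answers the trial's question. With about 19 unranked measures and several contrasts for each, nothing in the article separates a planned primary finding from the most favourable of many. The nominal 5% then does not describe the risk of a false claim, and the quoted detectable effects belong to a single test that the article never identifies.

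The article also takes two positions. The primary label and the talk of a proven effect are confirmatory. The Discussion describes a search for whichever measures respond. A reader of the results could not tell which standard of evidence applies.

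**Working it through.** **1. Reproduce the stated sensitivity.** Inputs: 91 participants in total and 72 in person (Participant recruitment and allocation), power 0.8, two-sided α = 0.05. Group sizes are in a figure not shown, so the splits are assumed. Noncentral t gives:

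| Comparison | Assumed n | Computed d | Stated d |
|---|---|---|---|
| Paired, all | 44 (45) | 0.432 (0.427) | 0.43 |
| Paired, in person | 32 | 0.511 | 0.51 |
| Between, all | 45/46 | 0.594 | 0.59 |
| Between, in person | 36/36 (32/40) | 0.670 (0.674) | 0.67 |

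The four figures are correct, each for one test at 5%.

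**2. Count the primary measures.** CDT 1, ALBA 1, ABACO 5, RAVLT 5 (A1, A1–A5 sum, B1, A5–A6, A6–A7), TMT 2, Digit Symbol 1, animal fluency 1: 16 cognitive. GDS 1, FAQ-CZ 1, NfL 1: 3 more. Total 16 + 3 = 19, before biochemistry and metabolomics. If ABACO is analysed as one score, the total is 19 − 4 = 15.

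**3. One two-sided test per measure, all nulls true.** If independent: 1 − (1 − α)^m = 1 − 0.95^19 = 0.623 (m = 15: 0.537). With a common correlation ρ, c = 1.96 and m = 19:

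1 − ∫ φ(u) [Φ((c − √ρ·u)/√(1−ρ)) − Φ((−c − √ρ·u)/√(1−ρ))]^m du

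For the favourable direction only, the second Φ term is dropped (2.5% per test).

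| ρ (assumed) | Either direction | Favouring probiotic |
|---|---|---|
| 0 | 62% | 38% |
| 0.3 | 52% | 27% |
| 0.5 | 41% | 20% |
| 0.7 | 28% | 14% |

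The either-direction figure is 52.5% at ρ = 0.3 and 46.9% at ρ = 0.4, so it falls below one half near ρ = 0.35.

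**4. Several contrasts per measure.** Simulation under the null: 36 per group, 19 measures, assumed between-visit correlation 0.7, 4,000 runs. The four contrasts are between groups at T3 and at T4, and the change within each group over its probiotic period.

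| ρ | T3 and T4 between, either direction | Four contrasts, either direction | Four contrasts, favourable |
|---|---|---|---|
| 0 | 81% | 97% | 85% |
| 0.3 | 72% | 93% | 70% |
| 0.5 | 60% | 85% | 59% |
| 0.7 | 44% | 70% | 44% |

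**5. Cost of keeping all 19 primary.** Bonferroni: 0.05/19 = 0.00263 per test. The between-group detectable d rises from 0.67 to about 0.94 in person (32/40), which is the figure relevant to the 16 cognitive measures. For measures using all participants it rises from 0.59 to about 0.83 (44/47). Power at the stated between-group d falls from 80% to about 39%.

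**The case against.** The other side has several good points.

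- **No any-measure success rule is written.** A reader might infer that one significant measure suffices. The sentence on two approaches compares brief tests with the battery and explains why both were used. It is not a decision rule. This stands.
- **Silence is not a decision against adjustment.** Multiplicity control is commonly left to an analysis plan, which is not shown. This stands for the adjustment method. It does not cover the choice of primary endpoint, which the protocol makes itself, by giving all these measures equal standing.
- **The study calls itself explorative.** True, and that would be a coherent position. It does not fit with a primary tier, directional hypotheses and talk of proof, so the article has to choose.
- **The measures overlap.** RAVLT A1 is part of the A1–A5 sum, and A6 enters two indices, so independence is the upper end of the range. It is also tempting to say that a false-positive probiotic effect is more likely than not. With one test per measure in the favourable direction, the figure never exceeds 38%.
- **The count depends on ABACO.** Its scoring is in supplementary material that is not shown, so 19 is conditional.
- **FAQ-CZ.** One might argue that it cannot improve, because entry requires preserved daily activities. The article gives neither an FAQ-CZ cut-off for entry nor baseline scores, so a ceiling is not established.

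**Conclusion.** The point holds as a defect in the definition of the primary outcome: about 19 scored measures plus biochemistry, metabolomics and other unnamed measures, no hierarchy, no primary time point, and sensitivity computed for one test. The stated d values are arithmetically right but are attached to no identified primary test.

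With one two-sided test per measure, the chance of at least one false positive is 28% to 62% for correlations from 0.7 down to 0, or 14% to 38% counting only results favouring the probiotic. The lowest either-direction figure is still more than five times the nominal 5%, and the lowest favourable-direction figure is more than five times its 2.5%. Adding time points and within-group tests raises both. These sizes rest on assumed common correlations, on five ABACO scores and, for the simulation, on assumed group sizes, between-visit correlation and contrasts. Whether the chance exceeds one half depends on those assumptions, so the result should be given as a range.

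**What to change.** Name one primary memory endpoint and one time point. A workable example is the RAVLT A1–A5 sum compared between groups at T3, tested at α = 0.05. T3 comes before the crossover, which has no washout, so carryover cannot affect it. Because Proposed analysis separates cognitive results by mode, the detectable d is 0.67 in person. It would be 0.59 only if that section were changed to pool in-person and online results.

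Make the remaining cognitive tests, GDS, FAQ-CZ and NfL secondary with Holm control, and metabolomics exploratory with false discovery rate control. List the biochemistry and other measures by name and assign each to a tier.

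The alternative is to relabel the whole tier exploratory and remove the confirmatory wording.

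The change is to wording only and needs no new data. The article dates the study from January 2021 to May 2022, so the hierarchy must be fixed before unblinding or be labelled post hoc. The downside is that fewer outcomes can be called confirmatory.

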##### Brief cognitive tests

Brief cognitive tests included the Clock Drawing Test (CDT), our newly developed the ALBA test, and a short cognitive battery (ABACO). The CDT was evaluated using our developed and validated scoring system called BaJa. It was weighted in favor of assessing clock hands and suppressing the contribution of the clock itself. It ranged from 0 to 5 points. The time of 23:20 was chosen as it is cognitively more difficult than 11:10 or 5:40, as proven in our report (Bartos et al., 2016). The CDT was used without modification in all testing sessions. The CDT was omitted in online testing.

The ALBA test is a newly developed three-minute examination of intentional and incidental short-term memory, which could differentiate patients with mild cognitive deficits from cognitively normal individuals. The innovative test paradigm was based on a recall combination of one short six-word sentence and six gestures. First, a participant was asked to remember a sentence. The following distraction included a demonstration of six gestures and their incidental and immediate recall. The final task was sentence recall (Bartos, 2019). Two alternate forms of the ALBA test are available with good comparable psychometric properties in the Czech Republic (Bartos and Diondet, 2020). Online ALBA was the same as the in-person one (Polanska and Bartos, 2022). A completed example of an ALBA form with detailed administration and evaluation instructions is shown in Supplementary Figure 1. The ALBA educational video is freely available at: https://www.youtube.com/watch?v=LyCuWc0-Gro.

Our in-house cognitive battery, ABACO, consists of five brief tests: (1) the Reading Encrypted Sentences subtest, (2) the sentence learning and recall, (3) verbal fluency test, (4) the PICture Naming and Immediate Recall (PICNIR), whose educational video is freely available at https://www.youtube.com/watch?v=cbJGtPG-nVA, and (5) the Five or Four-line test. Detailed information about them is in Supplementary material 3.

##### A comprehensive battery of neuropsychological tests

The Rey Auditory Verbal Learning Test (RAVLT) is intended for verbal memory evaluation. The test includes immediate verbal memory (A1), learning performance as a sum of five trials (A1–A5), proactive interference (B1), retroactive interference (A5–A6), and loss after consolidation (A6–A7) (Bean, 2011). In the Czech Republic, there are three alternative versions of RAVLT to eliminate the practice effect due to retest (Preiss et al., 2012). In the current study, we used them in version order: one at T1, two at T3, three at T4, and one at T5 (Figure 2). Online RAVLT testing was the same as that done in person.

The Trail Making Test (TMT) included parts A and B. Part A was used to evaluate processing speed, attention, and visuospatial ability. Part B, in addition to the mentioned functions, also assessed mental flexibility as a part of executive functions (Oosterman et al., 2010; Preiss et al., 2012). As there was no alternate form of the TMT in the Czech Republic, we used the same form for each test. The TMT was replaced with phonemic verbal fluency tests starting with the letters NKP during the online testing.

The Digit Symbol subtest from the Wechsler Adult Intelligence Scale III (WAIS-III) assessed the processing speed (Kaufman and Lichtenberger, 2005; Preiss et al., 2012).

Category (animal) fluency tests in person and online and phonemic fluency tests with initial letters NKP during online testing were used to evaluate executive functioning, language, and semantic memory (Lezak et al., 2012). Each verbal test took 1 min.

Online testing also included the Digit Span subtest from WAIS-III, which measured short-term verbal and working memory capacity (Preiss et al., 2012).

##### Self-report subjective questionnaires of depression and activities of daily living

Participants filled in the Geriatric Depression Scale (GDS) and the Functional Activities Questionnaire (FAQ-CZ) to assess their mood in the last 3 months and activities of daily living at each visit. The GDS ranged from 0 to 15 points, and FAQ-CZ ranged from 0 to 30 points. The more points, the more answers to depressive content in the GDS and the more impaired activities of daily living in the FAQ-CZ (Pfeffer et al., 1982; Lesher and Berryhill, 1994; Lach et al., 2010).

##### Biological surrogate markers of probiotic intervention

Serum, urine, and stool samples are taken for measurements of blood biochemistry, apolipoprotein E genotyping, metabolomic studies, and some brain-derived proteins and antibodies. The plan was to monitor metabolomics biomarkers, neurofilament light chain (NfL), and other measures and changes due to probiotic intervention. Participants provided their urine, fecal, and blood samples at each visit except the first one, as explained earlier.

#### Sample preparation

##### Serum sample collection and preparation

A nurse at each center took 13 ml of blood samples from participants who came for blood collection between seven and nine in the morning and who consumed their last meal the evening before. Blood was collected into two kinds of evacuated blood vacuum tubes (Vacuette 9 ml Serum and Vacuette 9 ml K3EDTA)—one for plasma and the second one for serum. After collection, the blood was immediately centrifuged at 4,000 rpm for 10 min, and the whole supernatant was transferred into a 5 ml Eppendorf tube, vortexed for 30 s, and divided into cryotubes for storage at -84^°^C till the analysis.

Before metabolomic High-Performance Liquid Chromatography Mass Spectrometry (HPLC-MS) analysis, one aliquot of serum (300 μl) thawed on ice, 600 μl of acetonitrile was added and vortexed for 30 s, and kept on ice for 10 min. Then, all samples were centrifuged at 13,500 rpm for 10 min at 4°C, and the liquid phase was transferred to vials for proper liquid chromatography-mass spectrometry (LC-MS) analysis.

##### Urine sample collection and preparation

A urine sample of 30 ml was collected on the same day in which study participants came for blood collection. We asked participants to take the first-morning urine for metabolomic purposes and consistency, specifically the second portion of their urine. They collected it into a sterile container, which they placed into a polystyrene transport box together with a freeze pack. When the participants bring their urine samples, they were centrifuged at 4,000 rpm for 10 min, then split into aliquots (500 μl) and stored at -84^°^C until the analysis.

Before metabolomic HPLC-MS/MS analysis, one aliquot of 500 μl urine was thawed on ice, 500 μl of acetonitrile was added, and it was vortexed for 30 s before being kept on ice for 10 min. Then, all samples were centrifuged at 13,500 rpm for 10 min at 4^°^C, and the liquid phase was transferred to vials for proper LC-MS analysis.

##### Stool sample collection and preparation

Each participant received a special toilet net during the first visit to avoid contact with stool and to prevent contamination from a toilet bowl. A participant took a stool sample of 1.5–2 ml from the central part of the participant’s stool immediately after defecation within 1 week before the planned visit. We provided them with special tubes we prepared in-house for this particular purpose. Our empty and filled tubes are shown in Figure 3. Stool samples were stored at -20^°^C in a home freezer. Participants brought them to the visit when the samples were stored at -84^°^C for proper long-term storage until the analysis.

**FIGURE 3 F3:**
[figure not shown]
Special in-house tubes before (left) and after (right) collection of one 1.5–2 ml stool sample.

Samples were thawed just before analysis. Stool pieces of a cherry stone size were transferred into polypropylene tubes, weighted, and the tubes were placed into a vacuum lyofilisator to dry all samples overnight. Each sample was weighed again, and a mixture of miliQ:MeOH: ACN (20:40:40) (v:v:v) was added in a ratio of 1:3 (stool weight: volume of mixture). Samples were placed into an ultrasound bath and sonicated for 20 min, followed by a 1 h incubation at 4°C. Finally, samples were centrifuged at 13,000 rpm for 10 min, and the supernatant was transferred into a vial for LC-MS analysis.

